### Data analysis

Statistical analysis will be performed using an intention-to-treat (ITT) approach. Baseline differences between groups will be tested using normality plots and the Kolmogorov-Smirnov test. Homogeneity between groups will be assessed using Levene’s test, thus ensuring successful randomisation. Missing data will be handled using the imputation method of the last observation carried forward. It will be decided to keep outliers in the analysis, as they may represent legitimate outliers or relevant information, which will be discussed in the future study.

A descriptive analysis of the dependent and independent variables of each group will be carried out. Quantitative variables will be expressed as mean ± standard deviation, while qualitative variables will be presented as frequency distributions and percentages.

To assess the effect of the interventions on the study variables in each group, multivariate analysis of variance (MANOVA) will be used as the main method. The variables will be grouped into two large blocks: those measuring functionality (HG, 5STS, GS, TUG, Two-minute step test and SPPB) and those measuring body composition (weight, WC, BF%, visceral fat, ASM, SMI and BMI). Subsequently, MANOVA will be performed on the difference in means after the intervention, using time as an intra-group factor and type of intervention as an inter-group factor. To graphically represent the MANOVA, the canonical Biplot will be displayed, including the confidence circles representing the set of variables in each intervention group. If the circles do not overlap, it can be concluded that there are significant differences between the groups.

To verify the results of the MANOVA, differences between groups for each quantitative variable, both functional and body composition, will be analysed using the repeated measures univariate analysis of variance (ANOVA) test for normal and homogeneous variables or the Kruskal-Wallis test for non-normal or heterogeneous variables. As an additional method, pairwise comparisons will be performed using Bonferroni’s test for normal and homogeneous variables and Dunn’s test for non-normal and heterogeneous variables to determine between which groups there are significant differences.

The effect size in ANOVA of the results obtained in each group will be measured by eta squared (η^2^). Values around 0.01 indicate a small effect size, around 0.06 a medium effect size, and 0.14 or more a large effect size.

A 95% confidence interval will be used to establish any differences, and statistical significance will be reported for all differences with p < 0.05 (bilateral). All statistical analyses will be performed using IBM SPSS for Windows (version 26.0, Armonk, NY. IBM. Corp.).

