**Methods:**

A randomized controlled trial will be conducted with three parallel groups: a PT group, a multicomponent training (MT) group, and a no-exercise group. The inclusion criteria will be women over 65 years of age who meet the diagnostic criteria for probable sarcopenia (Hand grip test less than 16 kg and Five Times Sit to Stand Test more than 15 s) according to the European Working Group on Sarcopenia in Older People (EWGSOP2). Two assessments will be conducted at the beginning and at the end of the 32 weeks of intervention, in which variables of body composition (muscle, fat and weight) and functionality (strength and physical performance) will be collected. There will be 3 sessions of 50 minutes per week in each intervention group. The masking strategy will be double-blind. The analysis of intergroup differences will be conducted using multivariate and univariate analysis of variance (MANOVA and ANOVA), as well as pairwise comparisons (Bonferroni corrections). Changes in the degree of sarcopenia and how many women eliminate the risk of sarcopenia (no probable sarcopenia) after the different interventions will be tested.

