### Sample/participants

#### Participants

All participants who voluntarily sign up for the GRP will be required to read and sign the informed consent form (See S1 File). The GRP is a project of the Faculty of Nursing and Physiotherapy at the University of Salamanca that offers older people in the city of Salamanca the opportunity to engage in physical exercise. Only those who meet all the selection criteria will be included.

The criteria for participation in the GRP are as follows: being female, over 65 years of age, residing in the community of the city of Salamanca, and meeting the diagnostic criteria for probable sarcopenia according to the EWGSOP2.

Exclusion criteria for participation in the study include previous participation in another exercise program, presence of fibrillations, uncontrolled cardiac pathology or hypertension, pacemaker use, history of severe trauma or recent surgery, congenital collagen involvement, severe mental illness, and any other circumstance that may interfere with the purpose or development of the study, as determined by the investigators. Elimination criteria during the intervention will include total attendance less than 85%, participation in other exercise programs during the intervention period, and changes in physical activity level outside the program.

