#### Sample size

Sample size was calculated for the main study variables, 5STS and HG. The minimum detectable change in similar populations and interventions was 2.5 points (a decrease in 5STS and an increase in HG) to consider a real change beyond measurement error [30, 31]. The study used GRANMO version 7.12 of April 2012. Assuming three groups, with an alpha risk of 0.05 and a beta risk of 0.2 in a bilateral contrast. A loss-to-follow-up rate of 20% was estimated, given that the intervention was extensive and older people are known to have lower adherence to physical activity programs [32]. It was concluded that 105 subjects would be needed among the three groups with a 1:1:1 ratio to detect a difference equal to or greater than 2.5 units, assuming a standard deviation of 5 units.

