### Procedures and data collection

#### Evaluations

Two evaluations will be conducted at the Faculty of Nursing and Physiotherapy of the University of Salamanca. The baseline assessment will take place after recruitment and before randomisation and allocation of subjects to the corresponding group. The preliminary assessment documents the independent variables and the primary outcome variables of the study. Intervention variables will also be recorded in detail and various objective tests will be applied. Subsequently, after randomization, different interventions tailored to each group will be carried out.

The final evaluation will be conducted at the end of the intervention period with no time intervals between evaluations. All tests will be performed by the same investigator in a standardized manner, as detailed in S2 Table. Investigators will be trained and have more than three years of experience in geriatric assessment. Results will be communicated through individualized, personalized reports to individuals who have indicated a preference to receive updates on results and progression at the outset.

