
All these outcome variables will be measured at baseline and at the end to check the change after the different interventions.

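### With outcomes measured only at baseline and at 32 weeks, last observation carried forward sets every missing final value to zero change. It shrinks the effect under the plan's own loss rate and can bias it either way if loss differs between arms.

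*Protocol article*

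**What the plan says.** The article fixes three things that have to be read together.

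- **Visits.** The abstract says "Two assessments will be conducted at the beginning and at the end of the 32 weeks of intervention". The Evaluations section repeats it ("Two evaluations will be conducted at the Faculty of Nursing and Physiotherapy") and adds "The final evaluation will be conducted at the end of the intervention period with no time intervals between evaluations". Description of the variables applies this to every outcome: "All these outcome variables will be measured at baseline and at the end to check the change after the different interventions".
- **Missing data.** Data analysis says "Statistical analysis will be performed using an intention-to-treat (ITT) approach" and then "Missing data will be handled using the imputation method of the last observation carried forward". It names no other method and no sensitivity analysis for missing data. The main analyses compare pre-post change between groups.
- **Expected loss.** Sample size says "A loss-to-follow-up rate of 20% was estimated". Participants adds "Elimination criteria during the intervention will include total attendance less than 85" per cent, participation in other exercise programmes and changes in outside activity. It does not say whether women removed for these reasons are re-tested at 32 weeks.

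**The concern.** Carrying the last observation forward presupposes a post-baseline observation to carry. Here there is none, so the rule is baseline carried forward, and every woman without a final test contributes a change of exactly zero.

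That value is hard to defend in this trial. Women enter because grip is below 16 kg and 5STS above 15 s, and the same two tests are the primary outcomes. Selection on extreme scores tends to produce some drift back towards the average at retest. Women who are re-tested can show that drift; women who are lost cannot. A woman who leaves because she has deteriorated is scored as stable.

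The stake is the size of the effect on both primary outcomes and on all secondary measures taken on the same schedule. The stated question of how many women leave the probable-sarcopenia category is also affected. A lost woman's carried-forward values are the ones that qualified her, so she is counted as not recovered whatever happened to her.

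**Working it through.** **Inputs from the Sample size section:** difference 2.5 units, SD 5 units, 105 women allocated 1:1:1, 20% loss.

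**Assumptions not in the documents:** the SD of 5 applies to the change score; loss is random within arm; control change is 0 unless stated; all arm-specific loss rates and any regression to the mean. Change is counted so that improvement is positive.

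**Women affected.** 105/3 = 35 per arm. 0.20 × 35 = 7 imputed and 28 observed per arm, or 21 imputed in all.

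**Formulas.** With a share d set to zero change and a true mean change m, an arm has mean (1 − d)·m and variance (1 − d)·25 + d(1 − d)·m².

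**Case 1: equal 20% loss, true difference 2.5, no control change.**

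- Estimate: 0.8 × 2.5 − 0.8 × 0 = 2.00, a 20% attenuation.
- Variance in the treated arm: 0.8 × 25 + 0.2 × 0.8 × 6.25 = 21.0. In the control arm: 0.8 × 25 = 20.0.
- Standard error: √((21.0 + 20.0)/35) = 1.08.
- Standard error from the 28 observed per arm: 5 × √(2/28) = 1.34.
- Simulation of 40,000 trials: coverage of the true 2.5 is about 92% with carry-forward and 95% with observed data only. Power is 44.5% against 44.7%.
- With no true effect and equal loss, type I error is 5%, even with 2 units of drift in both arms.

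**Case 2: unequal loss (illustrations, all inputs assumed).** With drift r in both arms and treatment effect e, the expected contrast is (r + e)(1 − d_PT) − r(1 − d_C).

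| Scenario | Expected estimate | Truth | Carry-forward rejects | Observed data reject |
|---|---|---|---|---|
| PT 30%, control 10%, r = 1, e = 2.5 | 3.5 × 0.7 − 1 × 0.9 = 1.55 | 2.5 | 28% | about 45% |
| PT 30%, control 10%, r = 2, e = 2.5 | 4.5 × 0.7 − 2 × 0.9 = 1.35 | 2.5 | 21% | about 45% |
| PT 10%, control 30%, r = 1, e = 0 | 0.9 − 0.7 = +0.2 | 0 | about 5.6% | 5% |
| PT 10%, control 30%, r = 2, e = 0 | 1.8 − 1.4 = +0.4 | 0 | about 6.7% | 5% |
| PT 30%, MT 10%, both truly improve by 2.5 | 1.75 − 2.25 = −0.5 | 0 | about 7% | 5% |

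In the first two rows, coverage of the true 2.5 falls to about 86% and 82%.

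**The case against.** Four counter-arguments deserve a fair hearing.

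- **The standard error.** A reader might infer that carry-forward understates it. It does not, for the quantity being estimated: in simulation the sampling SD of the carry-forward estimate and the mean reported standard error are both about 1.08. The comparison with 1.34 sets two different estimators side by side. What stands is that the interval is centred on the diluted value and too narrow for the real effect.
- **Power.** The 28% and 21% might be read against the planned 80%. The right comparator is the roughly 45% that observed data give in the same scenario. The gap between 80% and 45% comes from the sample size with these inputs and is a separate matter. With equal loss carry-forward costs no power. With the reverse loss pattern and a true effect it rejects more often, at 60 to 66%.
- **Invented inputs.** The article gives one overall loss rate. The 30%/10% split and the 1 to 2 units of drift are not in it, and drift cancels between arms when loss is equal. Unequal loss is plausible, because two arms face three sessions a week for 32 weeks under an attendance rule and controls face none. The documents do not establish it. The unequal-loss figures therefore show direction and order of size and are not predictions.
- **Conservatism.** Carry-forward is sometimes defended as cautious. Under equal loss it does shrink the effect. Under unequal loss it can create a difference where none exists, including between PT and MT.

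None of this supplies a post-baseline value to carry forward.

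**Conclusion.** The point holds and should be corrected before outcome data are analysed. It is not a detail left to a later plan: the article fixes a specific rule, as the only one, that does not fit its two-visit schedule.

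Under the plan's own 20% loss, with the assumptions listed, the harm is a 20% attenuation (2.0 for 2.5) and coverage of about 92%. Power and type I error are essentially preserved. Anything worse depends on loss differing between arms, which is assumed here.

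Three limits apply. The 20% is a planning figure; the actual share may be lower, or higher if women removed under the elimination criteria are not re-tested. The rule affects missing final values only, since a missing baseline has nothing before it to carry forward. If no arm truly changes on average and loss is random, the mean difference is not biased.

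**What to change.** In Data analysis, replace last observation carried forward as the primary method by one of the following:

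- a likelihood-based mixed model with baseline and final values as outcomes and baseline means constrained equal across arms, for 5STS, HG and the other univariate comparisons; or
- multiple imputation by arm from baseline values and age, with the imputed data sets also used for the MANOVA. Attendance can enter the imputation only within the exercise arms, because controls have no sessions.

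Add one delta-adjusted sensitivity analysis in which women without a final test are assumed to do worse than the model predicts. Keep baseline carried forward, if wanted, only as a sensitivity analysis under that name.

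No extra participants or visits are needed. The costs are somewhat wider confidence intervals and modest programming. The main extra work is pooling the MANOVA over imputed data sets, since the mixed model covers only the univariate comparisons.

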Five-Repetition-Sit-To-Stand Test (5STS): this is a functional test that assesses a person’s ability to stand up and sit down from a chair for five times without using the arms (lower extremity strength). The 5STS has been shown to be a more sensitive and specific measure than the original test [33]. It also offers excellent test-retest reliability (0.89) [34].Hand grip test (HG): is a quick, easy and inexpensive test that measures hand grip strength. This test is recognized in clinical practice and in the literature as a standard instrument for measuring HG [15]. It will be performed with the Jamar Plus device in standing position and with the elbow flexed to 90 degrees, which has been shown to have excellent test-retest reproducibility (r>0.80) and excellent inter-observer reliability (r = 0.98) [35, 36].**Secondary functional variables**: the Sarc-f questionnaire will be administered as a rapid diagnostic test for sarcopenia that predicts the need for further evaluation [37]. Physical activity will be monitored through the International Physical Activity Questionnaires (IPAQ) [38]. The Short Physical Performance Battery (SPPB), as it is a rapid, objective three-test physical function test that measures lower extremity strength, gait speed, and balance [39]. The Timed Up&Go (TUG), which is a predictor of frailty and falls, widely used in geriatric research to measure balance and mobility in older people [40]. Gait speed, which is a simple, objective and valid measure of human gait performance that has been used in a variety of settings and is recommended for use as a "vital sign" of health [41]. Two-minute step test to measure aerobic capacity in older adults [42]. The number of falls will also be recorded one year before the start and during the intervention.**Secondary body composition variables**: electrical bioimpedance (TANITA BC-418) will be used to measure most body composition parameters. The total percentage of fat (BF%) and muscle, which is important for general health, will be calculated [43]. Additionally, appendicular muscle mass (ASM) will be calculated, as it is one of the most important variables in the diagnosis of sarcopenia today. It is generally adjusted for height to obtain the appendicular muscle mass index (SMI) (ASM/height^2^). In order to predict the risk of developing chronic diseases, measurements of visceral fat, waist circumference (WC), and body mass index (BMI) (weight/height^2^) will be taken [15]. Height will be measured with a height rod.

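### Body-composition MANOVA: weight with BMI, and ASM with SMI, are near-duplicates on the change scale, which costs that block power and lets one change look like two agreeing results

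*Protocol article*

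**What the plan says.** The Data analysis section names MANOVA as the main method, applied to the change after the intervention with group as the between-subject factor. It forms two blocks:

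- **Functional:** "those measuring functionality (HG, 5STS, GS, TUG, Two-minute step test and SPPB" (six variables, including the two primary ones, HG and 5STS).
- **Body composition:** "body composition (weight, WC, BF%, visceral fat, ASM, SMI and BMI" (seven variables).

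Description of the variables labels body composition secondary. It gives BMI as weight over height squared. Of ASM it says "It is generally adjusted for height to obtain the appendicular muscle mass index (SMI", with the formula ASM over height squared. It describes SPPB as an "objective three-test physical function test that measures lower extremity strength, gait speed, and balance".

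After the MANOVA, each quantitative variable is tested separately in order to check the multivariate result, and all differences are reported at two-sided p < 0.05. The text does not mention that some variables in a block are computed from others.

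**The concern.** For a woman whose height does not change, the change in BMI is her change in weight divided by a constant; likewise for SMI and ASM. Heights differ between women, so the covariance matrix is not exactly singular and the MANOVA will run, but the second member of each pair is almost entirely predictable from the first.

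Two things are at stake. First, the multivariate test pays degrees of freedom for each variable whether or not it brings information, so the body-composition test is weaker than it need be. Body composition is part of the Aim, and the trial has only 105 women. Second, in the univariate tests and the biplot a single change in weight or in ASM is likely to appear as two agreeing findings, which makes an effect look broader than it is.

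**Working it through.** **Plan's own figure.** The protocol gives no power for either MANOVA. Its only related figure is the sample size, stated "with an alpha risk of 0.05 and a beta risk of 0.2 in a bilateral contrast" and "to detect a difference equal to or greater than 2.5 units, assuming a standard deviation of 5 units". The usual two-group formula gives n = 2(1.96 + 0.84)² × 5²/2.5² = 63 per arm. "A loss-to-follow-up rate of 20% was estimated", so 63/0.8 = 79 per arm and 3 × 79 = 237 in total, whereas the plan states "105 subjects would be needed among the three groups with a 1:1:1 ratio". The stated inputs alone therefore do not reproduce 105 as a total. That is a separate matter. Only the group sizes are used here: 105/3 = 35 per arm, and 35 × 0.8 = 28 after losses.

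**Step 1: how close the pairs are.** Assumptions not in the documents: mean height 1.55 m; height SD 0.06 m (range 0.04 to 0.08); change unrelated to height; SD of change 3 kg for weight and 0.8 kg for ASM. With mean change zero, the correlation of a change d with d/h² is 1/√(1 + CV²), where CV, the coefficient of variation of 1/h², is about 2 × SD(h)/mean(h).

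| Height SD | CV | Correlation |
|---|---|---|
| 0.04 m | 0.052 | 0.999 |
| 0.06 m | 0.077 | 0.997 |
| 0.08 m | 0.103 | 0.995 |

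Simulation agrees (0.9987, 0.997, 0.9946). With a mean weight loss of 2 kg the lowest value is 0.992. The share of variance not common to the pair is 1 − r², at most 1 − 0.992² = 1.6%. If height is measured again at the end, the second member gains mainly height-measurement error.

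**Step 2: degrees of freedom.** For Pillai's trace with three groups (the protocol does not name a statistic), the numerator df are 2p: 14 for seven variables and 10 for five, a difference of four.

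**Step 3: power at equal non-centrality (λ)**, that is, if the dropped variables carry no signal of their own:

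| N | λ | 7 variables | 5 variables |
|---|---|---|---|
| 84 | 12 | 53% | 61% |
| 84 | 18 | 75% | 82% |
| 105 | 12 | 54% | 62% |
| 105 | 18 | 76% | 83% |

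**Step 4: simulation** (Pillai's trace on change scores, 2,000 runs; effects and correlations assumed):

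| Scenario | Per arm | 7 variables | 5 variables |
|---|---|---|---|
| 0.3–0.5 SD on all five | 28 | 25% | 32% |
| ASM only, 0.6 SD | 28 | 28% | 35% |
| ASM only, 0.8 SD | 28 | 55% | 63% |
| 0.3–0.5 SD on all five | 35 | 37% | 44% |
| ASM only, 0.6 SD | 35 | 38% | 48% |
| ASM only, 0.8 SD | 35 | 67% | 77% |

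Under the null, rejection is 4 to 5% with either list.

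**Step 5: repeated findings.** In the scenarios with an effect, when weight was significant BMI was too in 92 to 95% of runs; for ASM and SMI it was 95 to 99%. In the null runs, where every significant result is a false positive, the figures were 87 to 92% and 94 to 98%. A chance finding would therefore usually be repeated as well.

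**Step 6: SPPB for comparison.** With the usual SPPB scoring categories assumed, its change correlates about −0.6 to −0.7 with 5STS change, and the other functional variables explain 51 to 59% of its variance. That is overlap, far from the near-identity in Step 1.

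**The case against.** **The loss depends on the inputs.** This stands. Where power is already high the gap shrinks: with a 1.1 SD effect on ASM and 35 per arm it was about 5 points (roughly 90% against 94%), and with effects spread over weight, WC, BF% and ASM it was about 1.5 points (98% against 99%). The direction was the same in every scenario run.

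**The block is secondary and nothing is biased.** Also right. A reader might infer that the test on the primary variables loses power, or that the MANOVA rejects too often. Neither follows: HG and 5STS are in the other block, and type I error does not move.

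**The protocol never calls the paired results independent confirmation, and it defines BMI and SMI openly as derived.** True. The point is only that testing each variable to check the MANOVA, without a word on the overlap, invites that reading.

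**SPPB.** A reader might infer that SPPB, 5STS and gait speed are likewise the same measurements entered twice. The article says which domains SPPB covers but not that it is scored from the same chair-stand or walking trials, and SPPB adds a separate balance test. Removing it is no clear gain. With no balance effect, power rises by about 3 to 5 points. With an assumed 0.5 SD balance effect in the MT arm (half that in PT), it falls from about 37% to 27%; at 0.7 SD, from about 48% to 27%. Table 2 gives MT a ten-minute coordination and balance component, so such an effect is plausible.

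**Conclusion.** The point holds for the body-composition block. Weight/BMI and ASM/SMI are near-duplicates on the change scale by the article's own definitions, given only that adult height is stable over 32 weeks. The near-identity is robust across the height SDs tried. The power cost, about 5 to 10 points at 28 to 35 per arm and less when power is near its ceiling, rests on assumed effects and correlations and should be read as an order of magnitude. The consequences are lost efficiency in a secondary block and apparent corroboration in the univariate results. The documents do not support extending the claim to the primary variables' block, to type I error, or to SPPB as a duplicate.

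**What to change.** In Data analysis, keep one of weight/BMI and one of ASM/SMI in the body-composition block, for example WC, BF%, visceral fat, SMI and BMI. Report the other two descriptively, marked as derived from the same measurement and not as separate confirmation. Make the choice before outcome data are seen.

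Leave SPPB in the functional block, and add that its result overlaps with 5STS and gait speed and is not independent confirmation of them.

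The cost is a sentence or two, with no new data, visits or participants. The small downside is that the two variables taken out (weight and ASM in the example) lose their place in the multivariate test.

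### The between-group model is not uniquely defined, the test switches on distributional checks, and baseline is not used as a covariate; one prespecified ANCOVA per outcome would settle all three

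*Protocol article*

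**What the plan says.** Four statements in the Data analysis section bear on the point.

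- **Main method.** The section says that "multivariate analysis of variance (MANOVA) will be used as the main method", applied to a functional block and a body-composition block. It then says "MANOVA will be performed on the difference in means after the intervention, using time as an intra-group factor", with intervention as the between-group factor. No covariate is named.
- **Univariate analyses.** Repeated-measures ANOVA is the "test for normal and homogeneous variables or the Kruskal-Wallis test for non-normal or heterogeneous variables". Pairwise comparisons follow the same split: Bonferroni on one branch, Dunn on the other.
- **Preliminary checks.** "Baseline differences between groups will be tested using normality plots and the Kolmogorov-Smirnov test". Levene's test is then described as "thus ensuring successful randomisation".
- **Reporting.** Differences are to be judged with 95% confidence intervals and two-sided p < 0.05.

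Elsewhere, Description of the variables and Evaluations give two measurements per outcome, at baseline and at the end. Sample size names 5STS and HG as the main variables and uses a difference of 2.5, an SD of 5, 105 women in a 1:1:1 ratio and 20% loss.

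**The concern.** The article itself fixes the model, the test-selection rule and the pre-tests, so these are not details left to an unseen analysis plan.

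With two measurements, a MANOVA of differences and a time-by-group model on raw values are separate specifications. The text combines them and does not say which term answers the trial's question. Nor does it say what the Bonferroni comparisons contrast. A comparison of group means averaged over both visits, which would halve the effect, is therefore not excluded.

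The switch to Kruskal-Wallis and Dunn means that 5STS and HG could be judged by different kinds of comparison, depending on a check made on the same data. The rank-based branch gives no adjusted mean difference with a confidence interval, although the plan relies on confidence intervals.

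Finally, baseline is collected for every outcome but enters no model as a covariate. In a trial with about 28 completers per arm, that can cost precision.

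**Working it through.** **1. The plan's own figure.** 105 / 3 = 35 per arm, and 35 x 0.8 = 28 completers per arm. The stated inputs do not lead to 105 by the standard two-group formula: n = 2(1.96 + 0.84)^2 x (5/2.5)^2, about 63 per arm; 63/0.8 rounds up to 79, and 3 x 79 = 237. That is a separate matter. Only the 28 per arm is used below.

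**2. What the model sentence can mean.** Let B be baseline and Y the final value.
- Change: D = Y - B, one value per woman. Time has no levels left, and the model is a between-group MANOVA (or ANOVA) of D.
- Repeated measures on (B, Y): the group-by-time interaction is the treatment test, and with two times it is equivalent to ANOVA on D.
- The group main effect of that same repeated-measures model compares means of (B + Y)/2. A true effect of 2.5 at the final visit appears there as (0 + 2.5)/2 = 1.25.

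The text names the factors but not the term, so the third comparison is not ruled out.

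**3. What the preliminary tests do.** Kolmogorov-Smirnov and normality plots assess distributional shape. Levene's test compares variances. Neither compares baseline levels between arms, and no test on the data can ensure that randomisation was carried out properly.

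**4. Kruskal-Wallis branch.** The text does not say whether changes or final values are ranked. A simulation with 28 per arm, one arm shifted by 2.5, raw SD 5 and 3,000 runs gave this omnibus power:

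| Correlation | ANOVA on change | Kruskal-Wallis on change | Kruskal-Wallis on final value | ANCOVA |
|---|---|---|---|---|
| 0.5 | 45% | 43% | 42% | 58% |
| 0.7 | 68% | 66% | 44% | 76% |
| 0.8 | 86% | 86% | 44% | 90% |

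Ranking changes costs little power; ranking final values can cost a lot. In both cases the quantity compared is no longer a mean difference.

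**5. Change score against ANCOVA.** Take raw SD s at both visits and baseline-final correlation rho.
- Variance of change: 2s^2(1 - rho).
- Residual variance in ANCOVA: s^2(1 - rho^2).
- Ratio, ANCOVA to change: (1 - rho^2) / [2(1 - rho)] = (1 + rho)/2, which is below 1 for any rho below 1.

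Pairwise power uses the noncentral t distribution with difference 2.5, n = 28 per arm, two-sided alpha 0.05/3 and 54 degrees of freedom. The noncentrality is 2.5 / (SD x sqrt(2/28)), and s = 5:

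| rho (assumed) | SD, change | SD, ANCOVA | Variance ratio | Power, change | Power, ANCOVA |
|---|---|---|---|---|---|
| 0.3 | 5.92 | 4.77 | 0.65 | 20% | 31% |
| 0.5 | 5.00 | 4.33 | 0.75 | 28% | 39% |
| 0.7 | 3.87 | 3.57 | 0.85 | 48% | 56% |
| 0.9 | 2.24 | 2.18 | 0.95 | 95% | 96% |

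Sample size does not say whether the SD of 5 refers to raw values or changes. If it is the SD of change, the variance ratio is the same. Pairwise power at unadjusted alpha 0.05 (normal approximation) is then 46% for change, against 64%, 58%, 53% and 48% for ANCOVA at rho of 0.3, 0.5, 0.7 and 0.9.

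**The case against.** The best defence is that the model sentence is only loosely worded. Outcomes are measured twice in order to examine change, and the factors are named as time within and intervention between. The natural reading is a time-by-group model, which can be fitted, is valid and gives the same test as ANOVA on change. This stands: a reader might infer that the planned analysis cannot be run, and the documents do not support that. What remains is that the deciding term and the pairwise target are not stated.

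Three other strong readings also go too far.
- **Baseline is ignored.** It is not: differencing uses it with the slope fixed at 1. What is absent is a baseline covariate.
- **Kruskal-Wallis necessarily discards baseline.** It does so only if final values are ranked, which the text leaves open. Which variable is ranked could fairly be left to a fuller plan. The data-driven switch of estimand cannot, because the article states it.
- **The plan tests time-averaged means.** At rho of 0.5 and 0.7 such a contrast would have about 9% and 8% power. The text does not state this analysis, so those figures describe a risk and not the plan.

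It is also fair to say that preferring ANCOVA is a matter of efficiency, that the gain depends on an unstated correlation and almost vanishes at 0.9, and that 28 completers is not the planned analysis set. The plan is intention-to-treat with last observation carried forward. That would analyse up to 35 per arm and give each woman lost after baseline a change of zero. All of this stands, and the power figures are illustrative for that reason.

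**Conclusion.** The concern holds in this form. The text leaves the main between-group test undetermined between two specifications, without naming the interaction or the pairwise contrast. It lets a distributional check choose the estimand for each outcome, including both primary variables. It makes a false claim about what the pre-tests show. These three points need no numerical assumption.

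The fourth point, no baseline covariate, is a loss of efficiency and not a bias: change-score analysis is unbiased under individual randomisation. The variance with ANCOVA is 35% lower at a correlation of 0.3, 25% at 0.5, 15% at 0.7 and 5% at 0.9. The matching gain in Bonferroni-level power runs from about 11 percentage points at 0.3 or 0.5 to about 1 at 0.9. This rests on an assumed correlation, 5 as the raw SD at both visits, completers only and independent women. The last assumption is doubtful: Design and setting of the study has women from the same senior centre grouped together before assignment. If centres are the unit assigned, the absolute power figures do not apply.

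This should be changed before the data are analysed. It does not by itself invalidate the trial.

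**What to change.** - For 5STS and HG, and likewise for each other quantitative outcome, prespecify one model: final value on arm plus the baseline value of the same outcome. Report the PT-MT, PT-CG and MT-CG contrasts, Bonferroni-adjusted, with 95% confidence intervals.
- If centres are the unit assigned, account for centre in the model with a small-sample correction.
- Do not let Kolmogorov-Smirnov or Levene results choose the test. Keep a rank-based, bootstrap or log-scale analysis as a sensitivity analysis only.
- If MANOVA is kept for the two blocks, run it on final values with the baselines as covariates, or on change scores with no time factor.
- Delete the clause about ensuring successful randomisation, and describe baseline by arm without tests.

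The cost is a little extra analysis work and a documented change to the stated main method. No new data are needed.
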